### Sample size and power calculations

Based on a survey of participating sites and recruitment so far, we estimate that about 1500 PWH will experience virological failure, including 900 on first-line and 600 patients on second-line or third-line ART. The number of individuals with DRMs will depend on the distribution across groups of patients initiating or switching to different lines of dolutegravir-based ART, the proportion switching with detectable VL and other factors.

For aim 1, we will have reasonable power to detect differences between HIV-1 subtypes. For example, comparing subtype C with subtype B and assuming a total sample of 250 in each group will allow us to detect a difference in the prevalence of resistance mutations of 3% vs 9% with 81% power. The test statistic used for these calculations (done in PASS 15^42^) is the two-sided Z-Test; the significance level of the test is 0.0500. The power will be lower for comparisons with other subtypes with fewer patients. For aim 2, with 1500 patients, we will have ample power to identify risk factors for virological failure in univariable and multivariable models. Power will be more limited for analyses of factors associated with the presence of InSTI DRMs. Assuming that 10% of patients on first-line ART, 20% on second-line ART and 30% on third-line ART will develop virological failure within 2 years, and further assuming that among patients failing first-line ART 1%–3% will develop InSTI DRMs, whereas 10%–20% of patients failing second-line and 20%–30% of patients failing third-line ART will develop InSTI DRMs, we can expect 84–157 patients with InSTI DRMs. As shown in figure 3 (from PASS 15^42^), in univariable analyses, we will have a power of 80% or above to detect risk factors with an odds ratio of 2 or above for a range of exposure prevalence.^43^ Power will be lower in the multivariable models, which should not include more than 5–10 variables.^44^

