**Methods and analysis:**

Nested within the International epidemiology Databases to Evaluate AIDS (IeDEA), DTG RESIST is a multicentre study of adults and adolescents living with HIV in sub-Saharan Africa, Asia, and South and Central America who experienced virological failure on dolutegravir-based ART. At the time of virological failure, whole blood will be collected and processed to prepare plasma or dried blood spots. Laboratories in Durban, Mexico City and Bangkok will perform genotyping. Analyses will focus on (1) individuals who experienced virological failure on dolutegravir and (2) those who started or switched to such a regimen and were at risk of virological failure. For population (1), the outcome will be any InSTI drug resistance mutations, and for population (2) virological failure is defined as a viral load >1000 copies/mL. Phenotypic testing will focus on non-B subtype viruses with major InSTI resistance mutations. Bayesian evolutionary models will explore and predict treatment failure genotypes. The study will have intermediate statistical power to detect differences in resistance mutation prevalence between major HIV-1 subtypes; ample power to identify risk factors for virological failure and limited power for analysing factors associated with individual InSTI drug resistance mutations.

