## Methods and analysis

DTG RESIST is a multicentre study enrolling PWH from sub-Saharan Africa, Asia, and South and Central America. Figure 1 summarises the study design. PWH who experience virological failure in routine care (confirmed or based on a single measurement) are enrolled in a dedicated study visit. At the study visit, they provide informed consent and a blood sample, which undergoes sequencing if the VL is above 1000 copies/mL. The DTG RESIST data are linked with the routine data collected within the IeDEA.

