### Outcomes and statistical analyses

We define two analysis populations to address aim 1 and aim 2: (1) all individuals who experienced virological failure on a dolutegravir-based first-line, second-line or third-line regimen in one of the participating cohorts and (2) all who started ART on a dolutegravir-based regimen or switched to such a regimen and were at risk of developing virological failure (the source population for (1)). The outcome of interest in population (1) will be any InSTI DRMs whereas in (2), it will be virological failure as defined above.

We will analyse population (1) using random-intercept logistic regression and population (2) using parametric survival models,^31^ stratified by treatment programme or country to account for heterogeneity across sites. We will measure the time from the date of switching to DTG-based ART (or from 6 months after initiating DTG-based first-line ART) to the earliest onset of virological failure, date of death or date of last follow-up visit. Exposure variables include age, sex, type of dolutegravir-based ART (initiated first line, switched to first line, second line or third line), previous exposure to InSTI drugs, pre-existing resistance mutations (from HIV-1 genotypes or predicted by the approach described below), advanced disease (as indexed by CD4 count <200 cells/µL), exposure to rifampicin, a history of ART interruptions and VL monitoring coverage and frequency (using approaches used in previous analyses^32 33^). We will follow recommendations on the conduct and reporting of prognostic research, including the choice of variables for inclusion in models and the handling of continuous variables and non-linear relationships.^34^ Missing values will be imputed using multiple imputations, assuming data are missing at random.^35^

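### The resistance outcome is defined and powered for all virological failures, but it is observed only in people whose study-visit sample is still above 1000 copies/mL and yields a sequence

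*Protocol article*

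**What the plan says.** Four parts of the protocol article bear on who contributes a resistance result.

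- **Analysis population.** Under Outcomes and statistical analyses, population (1) is "all individuals who experienced virological failure on a dolutegravir-based first-line, second-line or third-line regimen in one of the participating cohorts". Its outcome is any InSTI DRM.
- **Observation of the outcome.** The opening of Methods and analysis says that failure in routine care may be confirmed or rest on one measurement. Enrolment follows at a dedicated visit, where the person consents and gives blood, "which undergoes sequencing if the VL is above 1000 copies/mL". The abstract shortens this to "At the time of virological failure, whole blood will be collected".
- **Planning numbers.** The starting point under Sample size and power calculations is "we estimate that about 1500 PWH will experience virological failure". The article divides these failures into 900 first-line and 600 later-line cases. It assumes DRMs in 1–3% of the first-line group. For later lines its assumption reads: "10%–20% of patients failing second-line and 20%–30% of patients failing third-line ART will develop InSTI DRMs". The result is 84 to 157 people with DRMs. Figure 3 uses these two counts to support at least 80% power for an odds ratio of 2 over a range of exposure prevalence.
- **Missing data.** The only rule is general: "Missing values will be imputed using multiple imputations, assuming data are missing at random". It does not say whether the DRM outcome is included.

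**The concern.** Membership of population (1) is decided by a routine viral load. Its outcome depends on a second viral load, at a later visit, and on sequencing success. Someone who has re-suppressed by the visit belongs to the named population but can never have a result. The same holds for someone whose sample does not amplify.

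The main stake is the meaning of aim 1. A prevalence presented for all dolutegravir failures would describe people with persistent viraemia. If re-suppression goes with absence of resistance, that figure is higher than the prevalence among all failures. The stated limitations cover missing baseline genotypes, adherence data, subtype distribution and power, but not this selection.

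The second stake is the number of DRM cases. The 84 to 157 range makes no allowance for failures without a sequence.

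**Working it through.** **Inputs from Sample size and power calculations.** 1500 failures; 900 first line; 600 second or third line, with the split between those two not given; DRM rates 1–3%, 10–20% and 20–30%; two-sided alpha 0.05. The sequenced fraction *f* is not in the document, so every value of *f* below 1 is an assumption.

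**1. Reproducing 84–157.** With *t* third-line failures, cases = 900·p1 + (600 − t)·p2 + t·p3.

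- Lower end, t = 150: 900×0.01 + 450×0.10 + 150×0.20 = 9 + 45 + 30 = 84.
- Upper end, t = 100: 900×0.03 + 500×0.20 + 100×0.30 = 27 + 100 + 30 = 157.
- One common split of 125 to 140 third-line failures gives 81.5–83 and 159.5–161, within 3% of both ends.

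The range therefore counts all 1500 failures as having a result (*f* = 1).

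**2. If the unsequenced are free of DRMs.** The cases stay at 84 or 157 and only the denominator shrinks. Apparent prevalence = cases / (1500·f).

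| f | Denominator | Low scenario | High scenario |
|---|---|---|---|
| 1.0 | 1500 | 5.6% | 10.5% |
| 0.8 | 1200 | 7.0% | 13.1% |
| 0.5 | 750 | 11.2% | 20.9% |

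**3. If loss is unrelated to DRM status.** Cases = 84·f to 157·f: 76–141 at *f* = 0.9, 67–126 at 0.8, 59–110 at 0.7 and 42–79 at 0.5.

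**4. Power for an odds ratio of 2, low scenario, 20% exposed.** The unexposed risk p0 is solved so that the overall DRM rate equals cases/N, and p1 = 2·p0/(1 + p0). At *f* = 1 this gives p0 = 0.047 and p1 = 0.091. Two calculations are shown.

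- Wald: power = Φ(ln 2/SE − 1.96), where SE² is the sum of the reciprocals of the four expected cell counts. At *f* = 1, SE = 0.243 and power is 81%.
- Two-proportion Z-test with the same p0 and p1: 79% at *f* = 1.

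| f | Loss unrelated to DRM: Z-test / Wald | Only DRM-free people lost: Z-test / Wald |
|---|---|---|
| 1.0 | 79% / 81% | 79% / 81% |
| 0.9 | 75% / 77% | 78% / 81% |
| 0.8 | 70% / 72% | 78% / 80% |
| 0.7 | 65% / 67% | 77% / 80% |

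Taking the best exposure prevalence computed (40%), Z-test power in the low scenario is 86% at *f* = 1. With unrelated loss it is 78% at *f* = 0.8. With only DRM-free people lost it is still 84% at *f* = 0.5. In the high scenario with unrelated loss, best power is 95% at *f* = 0.8.

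**5. Subtype comparison.** A pooled two-sided Z-test of 3% against 9% with 250 per group gives 80.8%, which agrees with the stated 81%. It depends on the assumed 250 and is not derived from the 1500.

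**The case against.** Several points on the other side have force.

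- **The 1500 may already be net of attendance and consent.** It rests on a site survey and on recruitment so far, and over 750 people were already enrolled. This stands, so no deduction for refusal or non-attendance can be claimed with confidence. The viral-load condition at the visit and sequencing failure remain.
- **Failed amplification is partly covered.** Partial pol sequences including integrase are the fallback when viral load is too low for whole genomes. This reduces the loss but does nothing for samples at or below 1000 copies/mL.
- **The power claim cannot be fully tested.** Figure 3 is not shown. If the overall DRM rate is taken as the baseline probability, low-scenario power at 80% sequenced reaches up to 89%. The article also already calls power for DRM analyses limited. This stands: whether the 80% statement fails depends on a set-up that is not visible.
- **Exact analysis sets are often left to the full protocol.** That is true of detail, but here the article itself names a population for which its own sampling scheme cannot supply the outcome.

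Four stronger readings are tempting and are not supported:

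- *Power and prevalence are both damaged.* The power loss needs DRM cases to be lost in proportion. The prevalence inflation needs the lost people to be free of DRMs. Each weakens as the other holds.
- *The 81% subtype power is wrong.* Aim 1 works from viral sequences, so 250 per group is naturally read as sequenced people.
- *The plan will impute resistance for re-suppressed people.* The imputation sentence follows the exposure list and the modelling guidance, and it does not mention the outcome.
- *Resistance is certainly overstated.* That direction is plausible for re-suppression. For refusal, non-attendance or failed amplification, the document gives no basis for any direction.

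**Conclusion.** The mismatch is real. The article defines and sizes the DRM analysis on all failures, while its sampling scheme gives a result only for people above 1000 copies/mL at the study visit whose sample is successfully sequenced. Aim 1 prevalence must be read as applying to that group.

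The size is conditional, because the sequenced fraction is unknown. At an assumed 80%, either apparent prevalence is 7.0%–13.1% where 5.6%–10.5% would hold among all failures, with power almost unchanged, or expected cases are 67–126 and low-scenario power for an odds ratio of 2 at 20% exposure drops by about nine percentage points. The truth may lie between these two cases. The prevalence denominator is the more important issue, since it changes what aim 1 can conclude. The power point is secondary and confined mainly to the low scenario.

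**What to change.** 1. Define the DRM analysis set as participants with an integrase sequence from a study-visit sample above 1000 copies/mL, and label aim 1 prevalence accordingly. Bring the abstract's wording on the timing of blood collection into line.
2. Also report prevalence over all enrolled failures, counting people at or below 1000 copies/mL at the visit as without a detected DRM.
3. State that the DRM outcome is not imputed for those people. No one in that group is ever sequenced, so imputation could only borrow from viraemic participants.
4. Compare sequenced with unsequenced failures using the linked IeDEA data, with inverse-probability weighting as a sensitivity analysis.
5. Restate 84–157 and the power for an odds ratio of 2 on the expected sequenced number, using the sequencing yield among those already enrolled.
6. State that the 250 per subtype counts sequenced participants. The 81% then needs no change.

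The cost is a change of text, one descriptive comparison and one sensitivity analysis on linked data, with no new data collection. The stated power may become less favourable.

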**Figure 3 F3:**
[figure not shown]
Power versus exposure prevalence (%N) and OR for 84 (red) and 157 (green) patients developing InSTI DRMs. InSTI, integrase strand transfer inhibitor; DRMs, drug-resistance mutations.

The first PWH was recruited into the study on 13 June 2022 in Kanyama, Zambia. At the time of writing, over 750 PWH had been enrolled. Recruitment will continue until the end of May 2025.

### Patient and public involvement

There was no involvement of patients or the public in the development of the research questions or the study methods.

## Discussion

In low-income and middle-income countries, WHO recommends a public health approach to providing and monitoring ART,^45^,^48^ including standardised treatment regimens, simplified patient monitoring and clinical decision-making, population-level surveillance and monitoring of HIV drug resistance.^6 49^ WHO guidelines also recommend dolutegravir in first-line, second-line and third-line ART regimens.^8^ This multiplicity of roles of dolutegravir in the public health approach to ART, combined with limited access to VL and HIV drug resistance testing, may facilitate the emergence of dolutegravir resistance. DTG RESIST is a timely study addressing this threat.

DTG RESIST leverages the unique resource of IeDEA, a large international research consortium and rich resource for globally diverse HIV/AIDS data.^17^,^1950^ This brings four key strengths to the study: (1) pooling of data across a network of cohorts to explore patterns and determinants of a rare event, dolutegravir resistance; (2) inclusion of multiple HIV-1 subtypes across diverse geographical areas; (3) harmonised clinical and drug resistance data across participating sites and (4) combined expertise in the clinical, epidemiological, biological and computational fields required to assess the genotype–phenotype mapping. The many important collaborative publications of IeDEA highlight the strength of pooling data across multiple cohorts and regions.^3251^,^57^

DTG RESIST will generate whole HIV-1 genomes and develop robust laboratory procedures to amplify, sequence and assemble the genomes from the diverse set of HIV-1 strains obtained in the multiregional network.^27^ The spectrum of dolutegravir-selected mutations and their effects on phenotypic susceptibility in non-B subtypes is yet to be fully characterised. HIV-1 main group (group M) has diversified into nine subtypes (A–D, D–H and J–K), six subsubtypes (A1–A4 and F1–F2), multiple CRFs and thousands of unique recombinant forms.^58 59^ Most PWH are infected with non-B subtypes, but much of the evidence about ART outcomes and HIVDR is based on subtype B viruses from Europe and North America. HIV-1 subtype could influence treatment outcomes and the emergence of drug resistance.^60^,^62^ Finally, phenotypic testing of non-B subtype viruses with major InSTI resistance mutations and GWAS to explore the effect of mutations outside of the integrase will likely provide new insights into the relevant drug resistance pathways. Bayesian evolutionary models of accumulating mutations will be used to predict the expected genotype at treatment failure.^36^

There are also limitations to the approach. An important weakness is the lack of genotypic resistance data from before dolutegravir treatment for most participants. We considered collecting and biobanking samples from all people starting dolutegravir-based ART and then having paired samples from pretreatment and at the time of virological failure. However, this was not deemed feasible at most IeDEA sites. We will explore whether these missing baseline genotypes can be imputed by adapting models to predict expected resistance genotypes based on treatment and clinical history. Other challenges include the lack of harmonised data on adherence. There is uncertainty about the distribution of HIV-1 subtypes across sites, and the statistical power of the analyses of patterns and risk factors for dolutegravir resistance will be limited. We will consider pooling our data with those from other related studies to address these issues.^15^ The results of the GWAS and Bayesian network analyses may be subject to overinterpretation due to strong model assumptions and limited sample size. To avoid this, we will qualify these as preliminary and hypothesis-generating studies requiring validation.

## Ethics and dissemination

The research protocol was approved by the Biomedical Research Ethics Committee at the University of KwaZulu-Natal and the Ethics Committee of the Canton of Bern. All sites participate in IeDEA and have approval from their Institutional Review Boards (IRB) or Ethics Committees to contribute data to this research network. In addition, each participating site obtained ethics approval from their local ethics committee to conduct the specific additional data collection, including the determination of adequate provisions solicitation assent by adolescents or parental consent. The research findings will be shared through open-access publications and in dissemination meetings with local stakeholders, healthcare providers and communities.
